## Abstract

**Background:**

Promoting a healthy lifestyle (eg, physical activity, healthy diet) is crucial for the primary and secondary prevention of cardiac disease in order to decrease disease burden and mortality.

**Objective:**

The current trial aims to evaluate the effectiveness of the Do Cardiac Health: Advanced New Generation Ecosystem (Do CHANGE) service, which is developed to assist cardiac patients in adopting a healthy lifestyle and improving their quality of life.

**Methods:**

Cardiac patients (ie, people who have been diagnosed with heart failure, coronary artery disease, and/or hypertension) will be recruited at three pilot sites (Badalona Serveis Assistencials, Badalona, Spain [N=75]; Buddhist Tzu Chi Dalin General Hospital, Dalin, Taiwan [N=100] and Elisabeth-TweeSteden Hospital, Tilburg, The Netherlands [N=75]). Patients will be assisted by the Do Something Different (DSD) program to change their unhealthy habits and/or lifestyle. DSD has been developed to increase behavioral flexibility and subsequently adopt new (healthier) habits. In addition, patients’ progress will be monitored with a number of (newly developed) devices (eg, Fitbit, Beddit, COOKiT, FLUiT), which will be integrated in one application.

**Results:**

The Do CHANGE trial will provide us with new insights regarding the effectiveness of the proposed intervention in different cultural settings. In addition, it will give insight into what works for whom and why.

**Conclusions:**

The Do CHANGE service integrates new technologies into a behavior change intervention in order to change the unhealthy lifestyles of cardiac patients. The program is expected to facilitate long-term, sustainable behavioral change.

**Trial Registration:**

Clinicaltrials.gov NCT03178305; https://clinicaltrials.gov/ct2/show/NCT03178305 (Archived by WebCite at http://www.webcitation.org/6wfWHvuyU).

## Introduction

Cardiovascular diseases are the leading cause of death worldwide and a major driver of health care costs [1]. Evidence shows that a large proportion of the disease burden can be explained by behavioral factors (eg, low physical activity, unhealthy diet) [2], and that approximately 80% of heart disease, stroke, and type 2 diabetes can be prevented by attenuating or eliminating these health risk behaviors [3,4]. Hence, in their recent call for action, the American Heart Association stressed the importance of lifestyle management and called for better lifestyle counseling and the development of interventions to support health behavior change in cardiac patients [5].

Despite evidence showing that changing health behaviors improves (mental) health outcomes and lowers health care costs [5], to date, lifestyle counseling is not routinely implemented in physicians’ office [6]. More precisely, physicians provide this type of counseling in only 34% of the clinic visits [7]. One of the important reasons for this is the fact that face-to-face counseling is time-consuming.

Remote technologies offer a new delivery model for promoting healthy behaviors and are increasingly used in health care settings [8]. Although these new developments provide an excellent opportunity to deliver behavior change interventions to large groups of underserved patients, the reported effect sizes have been small [8]. Possible explanations for this are the short duration of the interventions [8], the limited number of health-related behaviors addressed within the intervention program [9], the mismatch between patients’ needs or preferences and the intervention, or the lack of sound behavior change methods adopted [10]. Previous trials within the cardiac population have demonstrated that a “one size fits all” approach does not seem to work [11]—revealing the importance of personalizing the care plan and addressing patients’ needs and preferences.

Evidence shows that the conventional way of providing education about a healthy lifestyle does not result in adopting desirable health behaviors [12]. In order to produce sustainable change in health behaviors, the Do Cardiac Health: Advanced New Generation Ecosystem (Do CHANGE) study will provide a personalized theory-based behavior intervention program for three months, creating awareness of unhealthy behaviors, addressing multiple health behaviors at the same time, and changing unhealthy habits. [13].

The Do CHANGE service aims to address cardiac patients’ unhealthy habits and change these by providing them with monitoring tools (eg, Fitbit) and increasing their behavioral flexibility. The Do Something Different (DSD) behavior change program will be provided, with the objective of disrupting the habit chains that are common in our daily living. Since people generally tend to live in accordance with their habits [14], disrupting these habits may lead to higher behavioral flexibility and eventually to behavior change [13]. The DSD program has been shown to be effective in changing health behaviors in previous studies targeting different populations [15]. The Do CHANGE service will, therefore, not only provide patients with innovative tools to support behavior change, but will also offer behavioral alternatives and carefully assess patients’ needs on using these innovative tools.

The objective of the current trial is to evaluate the effectiveness of the personalized Do CHANGE service in changing unhealthy lifestyle and improving the quality of life in cardiac patients. The Do CHANGE service will be developed and evaluated in three different countries (Spain, Taiwan, The Netherlands), in order to represent patients from different cultural backgrounds. This may contribute to a higher generalizability of the study findings.

## Methods

### Design

Do CHANGE is an international (Spain, Taiwan, The Netherlands), multicenter, randomized (intervention versus care as usual) controlled trial designed to support lifestyle change in patients with cardiac disease. By increasing patients’ behavioral flexibility and providing them with innovative devices, the objectives of enhancing lifestyle change and improving patients’ quality of life are expected to be reached. The evaluation of the Do CHANGE service delivery consists of two randomized controlled trials—trial 1 (Do CHANGE), which has been registered on www.clinicaltrials.gov (NCT02946281), has provided input for the further development and improvement of the currently described trial 2 (Do CHANGE 2, NCT03178305).

### Study Population

Patients primarily diagnosed with coronary artery disease (CAD) (having experienced a myocardial infarction, percutaneous coronary intervention, angina pectoris and/or coronary artery bypass graft surgery), symptomatic heart failure (HF) (New York Heart Association class I-IV), and patients diagnosed with hypertension (HT) will be included in the study. Hypertension is defined by values ≥140 mmHg of systolic blood pressure or ≥90 mmHg of diastolic blood pressure in two different measurements spaced 1-2 minutes apart and after 3-5 minutes in the sitting position. The values associated with the second measure will be used.

*Inclusion criteria:* Age 18-75 years, diagnosed (primary diagnosis) with CAD, HF or HT, having at least two of the following risk factors: smoking, positive family history, increased cholesterol, diabetes, sedentary lifestyle, and/or psychosocial risk factors. Patients should also have access to the Internet at home, have a smartphone which is compatible with the applications that will be used in the study (and have sufficient knowledge on using a personal computer and smartphone), and speak the countries’ native language.

Additional inclusion criteria for only HF patients include a diagnosis of systolic or diastolic heart failure and presence of HF symptoms (eg, shortness of breath, chest pain, and exhaustion).

*Exclusion criteria:* Significant cognitive impairments (eg, dementia), patients who are on the waiting list for heart transplantation, life expectancy <1 year, life-threatening comorbidities (eg, cancers), with a history of psychiatric illness excluding anxiety and/or depression, patients who do not have access to the Internet or a compatible smartphone, and patients with insufficient knowledge of the local language (Catalonian, Chinese or Dutch). Patients who have participated in the first phase of the Do CHANGE trial will also be excluded.

### Sample Size

A total number of 250 patients will be enrolled in the study at three participating centers (Badalona Serveis Assistencials, Badalona, Spain [N=75]; Buddhist Tzu Chi Dalin General Hospital, Dalin, Taiwan [N=100] and Elisabeth-TweeSteden Hospital, Tilburg, The Netherlands [N=75]). The sample sizes were determined based on the number of patients visiting the outpatient clinic per center.

One hundred and twenty-five patients will be enrolled in the intervention group and 125 in the control group. Considering participation rates in the previously performed Do CHANGE trial and other randomized controlled trials, we expect a significant number (50%) of patients to refuse participation. Hence, we will need to approach 500 patients. As the current trial aims to provide a proof of concept, sample size calculation will not be performed. A total of 250 patients is considered sufficient to meet this purpose.

### Randomization

Patients will be randomized (2:2) to either the intervention group or the control group (ie, usual care). Patients will be randomized using computerized block randomization (stacks of 4). The computer will generate randomization sequences that will be sealed by an independent researcher. Due to the nature of the study, the blinding of the researchers and health care providers is not possible.

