### Overall Procedure

The health care professional (cardiologist or cardiac nurse) will inform the patient about the study (orally and in writing). Patients who are willing to participate will be provided with an informed consent and will be given ten days to consider their participation. The research assistant will contact the patients by telephone and schedule a face-to-face appointment if they are willing to participate. During the face-to-face meeting, patients will sign the informed consent (together with the researcher) and will fill in the first set of questionnaires (shown in Table 1).

After completing the questionnaires, they will be randomized to either the intervention or “care as usual” group. Patients randomized to the intervention group will be provided with tools (as described in the “Intervention” section) and instructions on how to use them. Relevant tools and/or applications will be installed on patients’ mobile phone by the research assistant such that the patients will only have to charge the devices. One day after the face-to-face meeting, patients will be contacted by the research assistant by telephone to ensure that all devices are properly charged and that the system is functional. The full intervention (as described below) will be provided for three months. During this period patients will be contacted weekly by the research assistant to evaluate their progress (whether they are compliant or not with the treatment, they will receive feedback about progress).

**Table 1 table1:** Questionnaires.

Questionnaire	No. of items N=177	Construct	Assessment (month)		
			0	3	6
Health Promoting Lifestyle Profile [16]	52	Lifestyle	x	x	x
Do Something Different	45	Behavioral flexibility	x	x	x
World Health Organization quality of life questionnaire [17]	26	Quality of life	x	x	x
Unified Theory of Acceptance and Use of Technology [18]	28	Usability of tools; acceptance of tools; willingness to pay^a^			x
EuroQOL questionnaire [19]	5	Cost-effectiveness	x	x	x
Purpose designed^b^	4	Health care consumption	x	x	x
Patient Health Questionnaire [20]	9	Depression	x	x	x
Generalized Anxiety Disorder scale [21]	7	Anxiety	x	x	x
Distressed Personality scale [22]	14	Type D personality	x	x	x
Client Satisfaction Questionnaire [23]	8	Patient perceived satisfaction^a^			x

^a^These 3 constructs will only be assessed in the intervention group.

^b^Designed by the authors.

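### A single published block size of 4 in an open trial lets staff who book patients foresee some allocations: up to one third with per-site lists, about 4% with one shared list

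*Protocol article*

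**What the plan says.** The Randomization section of the protocol article sets equal allocation to the two arms, written as 2:2, and gives one block size: "Patients will be randomized using computerized block randomization (stacks of 4").

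On concealment it says: "The computer will generate randomization sequences that will be sealed by an independent researcher". It does not say whether there is one sequence per site or one shared by the three sites. On blinding it says: "Due to the nature of the study, the blinding of the researchers and health care providers is not possible".

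The Overall Procedure section assigns the roles. First contact is clinical: "The health care professional (cardiologist or cardiac nurse) will inform the patient about the study (orally and in writing"). After a ten-day period for consideration, booking passes to the research assistant: "The research assistant will contact the patients by telephone and schedule a face-to-face appointment if they are willing to participate". Randomization follows consent and the baseline questionnaires at that visit. For patients in the intervention group, "Relevant tools and/or applications will be installed on patients’ mobile phone by the research assistant", and the same role makes the follow-up calls the next day and every week.

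**The concern.** Sealing a sequence hides the list. It does not stop anyone from counting. In a block of 4 with two places per arm, the fourth allocation is always determined by the first three, and the third is determined whenever the first two agree. Someone who knows the block size and has seen the earlier allocations can deduce these without touching the seal. The article publishes the block size, and the role that books patients also handles the devices that mark the intervention arm.

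Staff who know the next arm can influence who is booked into that place, for instance by giving a device place to a patient who seems motivated or at ease with a smartphone. The between-arm primary outcomes (lifestyle, quality of life, behavioral flexibility) are questionnaires completed by the patients. Device data cannot check a between-arm difference, because under Primary Objectives only the intervention group has devices. The only covariate named under Statistical Analyses is baseline distress, so selection on motivation would not be adjusted for directly.

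**Working it through.** **Inputs.** From Randomization: block size 4, two places per arm, unblinded staff. From Sample Size: 75, 100 and 75 patients per site, 125 per arm. The article gives no predictability figure to reproduce. Its own counts agree: 75 + 100 + 75 = 250 = 125 + 125, and 250 / 0.5 = 500 to approach.

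**Certain allocations, list fully observed.** There are six equally likely blocks: AABB, BBAA, ABAB, ABBA, BAAB, BABA. In the first two, positions 3 and 4 are certain. In the other four, only position 4 is certain.

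- Per block: (2 × 2 + 4 × 1) / 6 = 4/3 certain allocations
- Share: (4/3) / 4 = 1/3 = 33.3%
- By position: 0, 0, 1/3, 1

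**Best guess, list fully observed.** The observer always guesses the arm with more places left. The chance of being right is 1/2, 2/3, 2/3 and 1 at positions 1 to 4. The mean is (17/6) / 4 = 17/24 = 70.8%, against 50% by chance.

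**Applied to the trial sizes.**

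- One list per site: 75 is 18 blocks plus 3 patients, so 18 × 4/3 + 1/3 = 24.33; 100 is 25 blocks, so 25 × 4/3 = 33.33. Total 24.33 + 33.33 + 24.33 = 82.0 of 250 (32.8%).
- One list, all sites' allocations seen: 250 is 62 blocks plus 2 patients, so 62 × 4/3 = 82.7 (33.1%).

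**One shared list, staff see only their own site but know the block boundaries.** Let *s* be the site's share of recruitment (0.3, 0.4, 0.3), with patients arriving in random order.

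- Position 3 is certain if both earlier places went to the same site and match: *s*²/3.
- Position 4 is certain if exactly two of the three earlier places are own-site and match, 3*s*²(1 − *s*)/3, or if all three are own-site, *s*³. The sum is *s*².
- Mean over four positions: (*s*²/3 + *s*²)/4 = *s*²/3.
- Weighted over sites: Σ*s*³/3 = (0.027 + 0.064 + 0.027)/3 = 0.118/3 = 3.9%. Simulation gives 3.8% to 3.9%, with a best-guess rate of 57%.

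**Undisclosed, randomly varying sizes.** Simulation of an observer who follows a whole list, knows which sizes are possible, and updates by Bayes' rule after each allocation:

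| Scheme | Certain | Best guess |
|---|---|---|
| Fixed 4, list fully observed | 33.3% | 70.8% |
| Random 4/6, list fully observed | about 5.7% | about 69% |
| Random 4/6/8, list fully observed | about 2.4% | about 68% |
| Fixed 4, shared list, own site only | about 4% | 57% |

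In the fully observed case, varying the size removes nearly all certainty but lowers best-guess accuracy by only about 3 percentage points.

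**The case against.** Several points on the other side stand.

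- **List structure.** A reader might infer that one third of allocations are knowable as a matter of fact. That requires per-site lists or sight of all sites' allocations. The plural in the Randomization section is compatible with per-site lists but does not establish them. The supportable range is about 4% to 33%.
- **Timing.** Randomization already follows consent and baseline questionnaires, which limits exclusion after assignment. No further step of that kind is needed.
- **Narrow route.** Under Study Procedure all eligible patients are to be approached, and a clinician informs them first. The research assistant's lever is therefore mainly the booking order of willing patients, which needs more than one patient waiting. The article also names a role, not a headcount, so one person need not know every allocation at a site.
- **Consequence.** A reader might infer that motivation at entry passes straight into the treatment estimate. The documents do not support that. The primary questionnaires are also taken at baseline (Table 1) and analyzed over time by a mixed model. Baseline scores do not remove unmeasured motivation, but no bias on any outcome can be calculated from the article.
- **Separate lists as a remedy.** If the present list is shared, moving to per-center lists with varying sizes would raise best-guess accuracy from 57% to about 68% for little gain in certainty.

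None of this removes the point. The freedom to choose whom to book next remains, the block size is fixed and published, and the remedy is cheap.

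**Conclusion.** The point holds as a modest, inexpensive design weakness. With per-site lists, or staff who see all allocations, up to one third of allocations (about 82 of 250) are certain in advance and 71% can be guessed. With one shared list and knowledge of the own site only, about 4% are certain and 57% can be guessed. Both cases assume that the observer knows the block size and where blocks begin, and tracks the allocations in view. The shared-list case also assumes recruitment in random order across sites.

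These figures measure predictability, not bias. Nothing in the article shows that selection occurred or would occur.

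**What to change.** For allocations not yet made, replace the fixed block of 4 with randomly varying block sizes, for example 4, 6 and 8, and keep the sizes from site staff. Keep the existing list structure: per center if it is already per center, shared if it is shared. State in the protocol which it is.

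With per-center lists, certain allocations fall from about one third to about 2%, while best-guess accuracy falls only from 71% to about 68%.

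The cost is regenerating the unused part of the lists and a possible imbalance of a few patients between arms (at most 4 on any list that stops inside a block of 8).

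The Results section expects data acquisition to end in summer 2018, so few allocations may remain. If none do, the report can still state the list structure and compare baseline characteristics between predictable and unpredictable positions.

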#### Exploratory Objectives

The current trial will also cover a number of exploratory objectives where the focus will be on 1) identifying subgroups of patients who might benefit the most from this intervention based on their profile (eg, psychological and/or disease profile); 2) evaluating the effects of the intervention on the electrocardiogram (ECG) data; and 3) gaining more insight in patients sleep patterns and physical activity over a prolonged period of time. These objectives will mainly serve the development of our new hypothesis regarding successful lifestyle change and will be tested using latent class analysis (LatentGold 5.0).

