### Intervention Versus Care as Usual

#### Intervention

The Do CHANGE intervention consists of different components, which can be used to provide care that meets patients’ needs. All patients included in the intervention group will be provided with the following technology: CarePortal, Moves app, Do Something Different (behavioral program), Beddit, Fitbit, blood pressure monitor, COOKiT, and Vire (the Do CHANGE app). In addition, disease-specific tools will only be provided to those who need them (ie, weight scale and/or FLUiT). Based on patients’ primary diagnosis (HF, CAD, or HT) the tools that might be useful will be recommended by the cardiologist. For example, patients with HF will receive a weight scale, since this can assist with monitoring sudden weigh gain, which might be an indication of deteriorating cardiac function. Figure 2 provides a schematic overview of the intervention components. To decrease patient burden, the COOKiT and FLUiT will be introduced to patients two months postbaseline measurement.

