The current trial might face some challenges due to the international scope and the number of devices that are given to patients. As patient recruitment will take place in Spain, The Netherlands, and Taiwan, cultural differences might affect the outcomes of the trial. Also, due to logistical differences between the pilot sites, patient recruitment will be slightly different per site. Although we do not expect this to have a significant impact on the results, we do consider it as a challenge. Secondly, some patients will receive multiple devices and/or apps that they are expected to use for 6 months. This might be perceived as overwhelming and may potentially lead to lower adherence. However, the current trial implements a behavior change component to the intervention, which aims to increase personal flexibility and enables behavior change. This might lead to more openness for new behaviors (using devices) and thus improve adherence.

Do CHANGE will provide insights into lifestyle changes and the possible mechanism that might drive this change. In addition, it will give valuable information from objective measures about patients’ behavioral patterns which, in turn, could serve as input for future studies that will focus on personalized medicine. This information will also provide input for the development of future ecological momentary interventions (real time interventions) that are focused on providing care to patients whenever and wherever they prefer it.

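### As written, neither the randomization nor the mixed model accounts for site or primary diagnosis, so the pooled comparison is open to avoidable chance imbalance or lost precision

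*Protocol article*

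**What the plan says.** The Randomization section of the protocol article fixes four things.

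- Ratio: "Patients will be randomized (2:2) to either the intervention group or the control group (ie, usual care".
- Method and block size: "Patients will be randomized using computerized block randomization (stacks of 4".
- Concealment: "The computer will generate randomization sequences that will be sealed by an independent researcher".
- Blinding: researchers and care providers cannot be blinded.

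It names no stratification factor. It also does not say that there is none, or that a single list serves every hospital.

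Under Sample Size, "A total number of 250 patients will be enrolled in the study at three participating centers", with targets of 75 (Spain), 100 (Taiwan) and 75 (The Netherlands), and "One hundred and twenty-five patients will be enrolled in the intervention group and 125 in the control group". Under Study Population, a primary diagnosis of CAD, HF or HT is an entry criterion, so site and diagnosis are both on record before allocation.

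The Statistical Analyses section evaluates treatment over time with a linear mixed model. Baseline distress is the only adjustment named, and the model is reduced to main effects when the interaction is not significant. The Discussion allows that culture could influence the results and notes that "patient recruitment will be slightly different per site", although the authors do not expect this recruitment difference to matter much. One exploratory aim is "identifying subgroups of patients who might benefit the most from this intervention based on their profile (eg, psychological and/or disease profile".

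**The concern.** Blocks of 4 keep the two arms level along whatever list they are drawn from. They do nothing for a factor that cuts across that list. If the list is shared, site is such a factor. Whether it is shared or kept per site, diagnosis is one.

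The article itself treats country as a possible influence on outcome, and diagnosis plausibly relates to lifestyle and quality of life. A factor of this kind can be balanced at allocation, adjusted for in the model, or both. The text as written does neither.

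At stake is the precision of the pooled comparison of the intervention with usual care. The two possible readings of the allocation lead to different losses:

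- **One common list:** the arms can differ by chance in their country mix, and no covariate corrects for it.
- **One list per site:** the country mix is balanced, but a model without site leaves between-country variation in the residual. The standard errors then do not reflect the balance that was achieved.

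**Working it through.** **The plan's own figures.** 75 + 100 + 75 = 250 and 125 + 125 = 250. With 50% refusal, 250 / (1 − 0.5) = 500 to approach, as stated. There is no power calculation to reproduce.

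**Case 1: one list for all sites.** With 125 of 250 patients in the intervention arm and sites entering in random order (assumption), the number treated at a site of size n is close to hypergeometric:

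SD = √[n × 0.5 × 0.5 × (250 − n)/249]

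- n = 75: √(18.75 × 175/249) = √13.18 = 3.63. The 95% range is 37.5 ± 1.96 × 3.63, about 30 to 45, so splits from 30:45 to 45:30.
- n = 100: √(25 × 150/249) = √15.06 = 3.88. The range is about 42 to 58.
- At a given 75-patient site, the chance of a gap of 9 or more patients is about 27%.

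A simulation with actual blocks of 4 (5,000 trials per scenario) agrees. A gap of 10 or more arises in about 16% of trials at each 75-patient site, in 24% at the 100-patient site, and in 38–40% for at least one site. The arms overall never differ by more than 2.

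**Effect on the pooled contrast.** A 45:30 split at one site gives site shares of 45/125 = 36% and 30/125 = 24%, a difference of 12 points. The standard error with 125 per arm is √(2/125) = 0.126 SD. The true difference between sites is not given. If that site differs from the other two by:

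| Assumed site difference | Shift = 0.12 × difference | Shift / 0.126 |
|---|---|---|
| 0.25 SD | 0.03 SD | 0.24 |
| 0.5 SD | 0.06 SD | 0.47 |
| 1.0 SD | 0.12 SD | 0.95 |

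These are shifts at the edge of the 95% range, not typical ones.

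**Case 2: one list per site.** The gap within a site falls to 1 at the 75-patient sites (75 = 18 × 4 + 3) and 0 at the 100-patient site (100 = 25 × 4). If the model omits site, the variance between sites stays in the error term. For one site holding 75/250 = 0.3 of patients and differing by d, that variance is 0.3 × 0.7 × d², in units of the within-site variance:

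- d = 0.5: 0.0525, so the standard error of a between-patient contrast is too wide by a factor of √1.0525 = 1.026.
- d = 1.0: 0.21, factor √1.21 = 1.10.

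**Diagnosis.** The mix is not given. It was assumed to be one third each, then 50/20/30%. The 95th percentile of the between-arm difference in a diagnosis share is about 10–12 points. The chance that some diagnosis differs by 10 points or more is about 18–22%, whether lists are common or per site. With a 0.5 SD difference between diagnoses (assumed), 10–12 points shift the contrast by 0.05–0.06 SD.

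**Where it enters the model.** If month 0 is among the modelled time points, a stable level difference between sites or diagnoses largely drops out of the group-by-time term. It goes straight into the group main effect, which is what remains when a non-significant interaction is removed.

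**The case against.** The strongest reply is that the article is condensed. It uses the plural for its sequences, and patients are randomized after a face-to-face visit at hospitals in three countries, so per-site lists are a natural reading. The full protocol may name strata. This stands: a reader might infer that randomization is unstratified, but the text does not say so, and the single-list figures are conditional. It does not remove the point. If lists are per site, the named model leaves out the stratum, and diagnosis remains unaddressed on either reading.

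Three further inferences are tempting, and the document does not support them.

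- **Diagnosis-dependent tools bias the comparison.** Diagnosis does guide some equipment ("the tools that might be useful will be recommended by the cardiologist"), but this concerns only add-ons, the weight scale and FLUiT, within the intervention arm. The core set is common to all intervention patients. The add-ons neither cause nor worsen imbalance between arms.
- **Country and disease-profile comparisons suffer most.** The statistical section plans no country contrast, and the disease-profile work is exploratory and uses latent class analysis. Within a 75-patient site, a 45:30 split keeps 4 × 45 × 30/75² = 96% of the efficiency of an even split, and 42:33 keeps 98.6%. Small subgroup size is the real limit there.
- **Nine site-by-diagnosis strata are needed.** With a fixed block of 4 and unblinded staff, nine short lists would make assignments easier to guess locally than a shared list would. Covariate adjustment handles diagnosis without that cost.

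It is also fair to say that an ordinary confidence interval already allows for chance imbalance. That is why the issue is precision and not validity. It is not a reason to leave out two known covariates that cost almost nothing to include.

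**Conclusion.** The point holds in a limited form. As the article stands, site and primary diagnosis are known at entry but used in neither the allocation nor the model. The consequence is chance imbalance and lost precision in the pooled contrast. The comparison remains unbiased on average.

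For an assumed 0.5 SD difference between sites, the size is a shift of up to about 0.06 SD at the 95% limit with one list (standard error about 0.13 SD), or a standard error about 3% too wide with per-site lists. Both scale with the site effect, which the article does not give. The diagnosis figures also depend on an assumed mix. The loss is smaller if the effect is read from change since month 0, and applies in full if it is read from the group main effect. It is modest, but it can be avoided at almost no cost.

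**What to change.** In Statistical Analyses, add site (three levels) and primary diagnosis (CAD, HF, HT) as fixed factors in the linear mixed model, alongside baseline distress. This corrects level differences if one list was used and matches the analysis to the allocation if lists were per site. It holds whichever way patients are allocated.

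In Randomization, state that the independent researcher generates a separate block sequence for each site. If this is already done, saying so is enough. Diagnosis strata within site are optional.

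**Cost.** Four more model parameters (two for site, two for diagnosis), three sealed sequences, and a sentence in each section. No extra patients or visits are needed. If the site targets are met, the two incomplete blocks leave the arms at 125:125 or 124:126. If sites stop off target, each can add a gap of at most 2, so at most 6 overall. Per-site lists with a fixed block of 4 are somewhat easier to predict locally than a shared list, so the sealing of the sequences matters.
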